#### 8.2.4 Physical examination

Physical examination is performed at screening and considered as baseline data, afterwards the final physical examination is performed at cessation of CRRT by identical researcher. Physical examination contains allergic, cardiovascular, pulmonary, gastrointestinal, hepatic, endocrinologic, renal, genitalial, musculoskeletal, skin, connective tissue, neurologic psychological and other examination.

Notable disturbance during physical examination at screening is recorded in physical examination section of data sheet. After initiation of CRRT, notable disturbance that can be identified as adverse event should be noted in the adverse event section of data sheet. However, if the abnormal physical examination was redundant as screening, it should be recorded in physical examination.

#### 8.2.5 Pregnancy test and Clinicopathologic examination

Pregnancy is confirmed by urine HCG test in female of childbearing age without sterilization operation or menopause (including surgical menopause) at screening.

Clinicopathologic test is performed in all patients and evaluates patient's general condition. All patients are required to perform pregnancy test, clinicopathologic test and confirm inclusion/exclusion criteria.

Clinicopathologic test is performed at screening and at the cessation of CRRT. When researcher considered it necessary, additional examination is possible.

Hematologic, biochemical, arterial blood gas, lipid, blood coagulation test is performed every 72 hours after initiation of CRRT. If CRRT is discontinued within 72 hours, examination is performed at the time of cessation. Urinary test is performed at screening and cessation. Specific coagulation test is performed at screening. When the patients deceased during CRRT and the examination at discontinuation were not performed, the examination right before the death can be used.

Examination includes as follows;

- Hematologic: Hemoglobin, Hematocrit, RBC, WBC, Platelet, differential count, ESR
- Biochemical: Alkaline phosphatase, BUN, Creatinine, SGPT (ALT), SGOT (AST), Total bilirubin, Uric acid, Na, K, Cl, Ca, P, CRP, total CO2
- Arterial Blood Gas: O2, CO2, arterial pH, HCO3, Base excess/deficit, Oxygen saturation
- Lipid: Cholesterol
- Urine analysis: pH, Protein, Glucose, Ketone, WBC, RBC
- Coagulation test: aPTT, PT-INR
- Specific coagulation test: fibrinogen, fibrin degradation product
- Pregnancy test: urine HCG test

#### 8.2.6 Central venous pressure monitoring

Central venous pressure is monitored every 24hours during CRRT.

#### 8.2.7 Severity evaluation

Patient's disease severity is evaluated using Acute Physiology and Chronic Health Evaluation II (APACHE II) and severity of acute renal failure is categorized by Cleveland Clinical Foundation score (CCF score) and RIFLE criteria (enclosure 7,8,9). BUN/Cr values used to assess the CCF score and RIFLE criteria is done at screening.

#### 8.2.8 Filter life span

To check filter life span, every filters used during CRRT was checked for initiation time, discontinuation time, and the reason for filter failure.

The reason for filter failure is categorized as follows;

- ① Due to filter clot
- ② Ultrafiltrate loss is less than 150mL/hr in recent 3 hours
- ③ Persistent transmembrane pressure > 200mmHg
- ④ Vascular access abnormality
- ⑤ Extracorporeal circuit abnormality
- ⑥ Due to another apparatus (such as radiologic examination)
- ⑦ Etc.

#### 8.2.9 Subject suitability assessment

By physical history and basic investigation data, patients that are fit to section 6.1 inclusion criteria and section 6.2 exclusion criteria are screened after voluntarily agreed to consent. After screening, all results are put together to finally evaluate whether the patients are appropriately enrolled.

#### 8.2.10 Randomization and prescription of study medication

Patients who are fit to inclusion/exclusion criteria are randomly assigned to futhan and no-anticoagulation group as described by section 7.5 and study medication was administered. Randomization is performed after the subject suitability assessment was conducted and when the initial administration of nafamostat mesilate is done, it is continued until discontinuation of CRRT.

#### 8.2.11 Identification of change in medication history

When there is alteration in medication compared to the medication at screening, it is investigated and documented in the case report.

#### 8.2.12 Collection of medication and checking compliance

The rest of the medication that remains after administration is recorded.

#### 8.2.13 Checking adverse events

Patients are repeatedly educated to report any information of adverse events, and researchers are obligated to investigate adverse events by interview and physical examination. When investigating adverse events, date of manifestation, disappearance, severity, actions that took step related to the study medication, relation with the study medication, any medication that is suspected to have relations with the adverse events except the study medication and treatment related to adverse event was sought.

The typical symptoms that are classified as adverse events are described as follows.

(1) Fever

Fever is checked by documenting body temperature, its severity is investigated, and finally the relationship between the medication and symptom is evaluated.

(2) Subjective and objective symptom

Subjective and objective symptom is investigated through the researcher's examination, its severity is investigated, and finally the relationship between the medication and symptom is evaluated.

(3) Clinicopathologic examination

Any abnormality of clinicopathologic examination is followed until it is recovered, and the predicted cause is evaluated.

#### 8.2.14 Checking renal function

After discontinuation of CRRT, patients were sought whether he or she continued hemodialysis and BUN/Creatinine is checked to evaluate renal recovery at the first outpatient department visit after discharge.

#### 8.2.15 Checking Mortality

After discontinuation of CRRT, patients were sought whether he or she died and mortality at 28 days after initiation of CRRT was checked.

#### 8.2.16 Blood loss

After initiation of CRRT, amount of blood loss at filter exchange was examined.

#### 8.2.17 Transfusion

After initiation of CRRT, transfusion is performed when hemoglobin is under 7g/dL or under 10g/dL and shows hemorrhage. Also, free frozen plasma or platelet concentrate is provided whenever is necessary.

### 8.3 Observation method (per visit)

#### 8.3.1 Screening

Patients who are selected for this study is explained about the study and evaluate as following order

- ① Before enrollment, patient is explained of the study procedure, and signs the written consent.
- ② Patients are given a screening number in order.
- ③ Patient's demographic information and medical history (past and current medical history including surgical history) are sought.
- ④ Vital signs are checked
- ⑤ Physical examinations are performed.
- ⑥ Clinicopathologic examinations are performed.
- ⑦ Pregnancy test is performed, if the patients is female of childbearing age.
- ⑧ Patient's severity was evaluated using CCF score, RIFLE criteria, APACHE II.

#### 8.3.2 Medication phase (randomization and after initiation of CRRT)

- ① After screening, change in medication history is checked.
- ② Every examination including clinicopathologic test and assessment is collected to finally evaluate the patient's suitability as a subject.
- ③ Patient is given a randomization number by random enrollment.
- ④ Study medication is administered.
- ⑤ Hematologic examination was conducted every 72 hours after initiation of CRRT.
- ⑥ Vital sign (blood pressure, body temperature, pulse rate, respiratory rate) is assessed every 4 hours after initiation of CRRT.
- ⑦ Filter life span and reason for discontinuation is sought.
- ⑧ Blood loss is checked at filter change after initiation of CRRT.
- ⑨ Transfusion (packed RBC, free frozen plasma, platelet concentrate) is assessed after initiation of CRRT.
- ⑩ Any changes in medication are recorded.
- ⑪ Adverse event is investigated.
- ⑫ Bleeding accident is checked.

### 8.3.3 Study completion or discontinuation

The following examination is conducted when the subject has completed or discontinued the study. When the study was discontinued due to subject's death, examination before death is used.

- ① Vital sign is checked.
- ② Physical examination is conducted
- ③ Clinicopathologic test (hematologic, hematochemical, lipid, blood coagulation, blood gas, urine test) is conducted.
- ④ Any difference in medication is assessed.
- ⑤ Adverse event is investigated.
- ⑥ Remaining medication is collected, checked and documented.

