#### 7.4.2 Medication that are prohibited to use in combination

The medications listed as following are not allowed to use in combination with nafamostat mesilate.

- ① Medication in similar effect: warfarin, urokinase, FOY, aprotinine, dextrin, prostaglandine etc.

② Anticoagulation medication: heparin, citrate, hirudine etc.

When the patient is needed to use medication that are prohibited to use in combination with nafamostat mesilate under researcher's approval, the patient is excluded from the study immediately and an accurate and detailed documentation should be noted at the last page of the clinical report.

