## 8. Observation, clinical examination and observation method

### 8.1 Clinical study schedule

| Period                                        | Screening | Treatment  | Closing  | Follow-up  |
|-----------------------------------------------|-----------|------------------------|----------------------|------------------------|
| Written consent                               | X         |                        |                      |                        |
| Authorize a Screening number                  | X         |                        |                      |                        |
| Demographical analysis                        | X         |                        |                      |                        |
| Personal/Drug history survey                  | X         |                        |                      |                        |
| Vital sign check                  | X         | X                      | X                    |                        |
| Physical examination                          | X         |                        | X                    |                        |
| Pregnancy test                    | X         |                        |                      |                        |
| Clinicopathologic examination     | X         | X          | X                    |                        |
| Severity analysis                             | X         |                        |                      |                        |
| Filter life span                              |           | X                      | X                    |                        |
| CVP monitoring                                |           | X                      |                      |                        |
| Subject compatibility assessment  |           | X                      |                      |                        |
| Randomization                                 |           | X                      |                      |                        |
| Drug administration                           |           | X                      |                      |                        |
| Check difference in drug dosage               |           | X                      | X                    |                        |

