| Adverse event check                           |           | X                      | X                    |                        |
| Residual renal function check     |           |                        |                      | X                      |
| Mortality check                               |           |                        | X                    | X                      |
| Blood loss                                    |           | X                      | X                    |                        |
| Packed RBC transfusion                        |           | X                      | X                    |                        |
| Free frozen plasma, Platelet      |           | X                      |                      |                        |

1: administered until treatment is concluded

2: If patients are improved, closing examination was performed at discontinuation of CRRT. However, if the patient has deceased, the last examination before death was used.

3: Body temperature, pulse rate, respiratory rate, blood pressure was examined before other examination was performed. During CRRT, vital sign was examined every 4 hours. At screening, body temperature was examined rectally.

4: Pregnancy test was performed in female without sterilization or any effective contraception in child-bearing age.

5: Detailed examination was as following;

- Hematologic: Hemoglobin, Hematocrit, RBC, WBC, Platelet, differential count, ESR
- Biochemical: Alkaline phosphatase, BUN, Creatinine, SGPT (ALT), SGOT (AST), Total bilirubin, Uric acid, Na, K, Cl, Ca, P, CRP, total CO2
- Arterial Blood Gas: O2, CO2, arterial pH, HCO3, Base excess/deficit, Oxygen saturation
- Lipid: Cholesterol
- Urine analysis: pH, Protein, Glucose, Ketone, WBC, RBC
- Coagulation test: aPTT, PT-INR
- Specific coagulation test: fibrinogen, fibrin degradation product

During CRRT, Clinicopathologic examination was performed every 72 hours. If CRRT was discontinued before 72 hours, examination was performed at discontinuation. Uine analysis was performed at screening and closing. Specific coagulation examination was substituted for the examination performed recently

6: Subject compatibility assessment was performed based on all examination, personal history and inclusion/exclusion criteria. Patients who were fit in these criteria was enrolled as subjects.

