### 8.3.4 Follow-up

Follow-up investigation includes recovery of renal function, patients' mortality. When patient's condition is improved and CRRT is not necessary, patient is followed whether he or she is on dialysis at discharge, and renal recovery is sought at 1st outpatient department visit after discharge. Also, mortality at discharge and 28 days after initiation of CRRT is investigated. Follow-up investigation is conducted according to patient's outpatient department visit schedule and no extra-visit for the study is planned.

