## 10. Study discontinuation, drop out, or analysis exclusion criteria

## 10.1 Study discontinuation and drop out criteria

All patients who enrolled in the study should be recorded of the completion of the study, and if the medication is discontinued or observation is stopped, the reason is recorded. The criteria for patient's drop-out are as follows.

- ① Circumstance that violates inclusion/exclusion criteria
- ② Serious adverse events occurred in patients or patients demands to be dropped out of the study due to adverse events.
- ③ Patient or legal guardian demand the discontinuation of the study due to unsatisfactory curative value during the study.
- ④ Severe hemorrhage
- ⑤ Critical violation of study protocol by principal investigator, researcher or patients.
- ⑥ Patients or legal guardian's withdrawal of the consent.
- ⑦ When patients cannot be followed.
- ⑧ When the patient takes a medication that can influence the study result, without the researcher's authorization during study period.
- ⑨ When the patient is decided not fit for the study progression by researchers.

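### Patients dropped from the study for treatment-related events have no stated outcome follow-up, and their closing time is undefined if CRRT continues

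*Protocol*

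**What the plan says.** - **Section 10.1** asks that "if the medication is discontinued or observation is stopped, the reason is recorded". It continues "The criteria for patient's drop-out are as follows" and gives a single list of nine. Serious adverse events, severe hemorrhage and the researcher's judgement stand there beside withdrawal of consent and inability to follow the patient.
- **Section 7.4.2**: when a prohibited medication becomes necessary, "the patient is excluded from the study immediately".
- **Section 8.3.3**: "The following examination is conducted when the subject has completed or discontinued the study". Six items follow: vital signs, physical examination, laboratory tests, medication changes, adverse events and remaining drug.
- **Section 8.1, Closing column**, marks "Filter life span", "Mortality check", blood loss and packed red cells. Note 2 sets the time: "If patients are improved, closing examination was performed at discontinuation of CRRT". For a patient who died, it uses the last examination before death.
- **Section 8.3.4**: a patient whose condition "is improved and CRRT is not necessary, patient is followed whether he or she is on dialysis at discharge". The same section then provides for mortality at discharge and at 28 days from the start of CRRT, without that condition. Note 7 to the schedule and section 8.2.15 also provide for mortality follow-up.
- **Section 11.3.1** makes the per-protocol analysis principal for efficacy. It limits the ITT set to patients whose vital status is confirmed (in the futhan group, also to those dosed at least once) and allows last observation carried forward after drop-out.

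**The concern.** Stopping an assigned treatment and ceasing to be observed are different events. A patient who bleeds, or who needs another anticoagulant, can stop nafamostat and still be observed to death or discharge. Where the protocol turns such an event into study exit and does not say that recording continues, staff who follow it as written may stop collecting.

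The reasons concerned are related to prognosis and plausibly to arm. The study is open-label, and section 7.4.2 is worded in terms of combination with nafamostat. Missing outcomes would therefore be unlikely to fall at random. At stake are filter life (the subject of the trial's title), blood loss and transfusion after drop-out and, if vital status is not pursued, ICU mortality. An analysis plan cannot recover data that were not recorded, so the matter belongs in the protocol.

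**Working it through.** **1. Is a dropped patient kept under outcome recording anywhere?** Section 10.1 requires the reason. Section 7.4.2 requires documentation of the exclusion. Section 13.3 provides other treatment and access to care. Section 8.3.3 requires six examinations. None of them says that outcomes are recorded after exit.

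**2. When is closing?**

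| Situation | Schedule, note 2 | Section 8.3.3 |
|---|---|---|
| Improved, CRRT ends | end of CRRT | completion |
| Death | last examination before death | examination before death |
| Leaves the study, CRRT continues | not covered | on leaving |

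The first two rows can be reconciled, since sections 8.2.4 and 8.2.5 also place the final examinations at the end of CRRT. The third cannot. If closing is at exit, filters, blood loss and transfusions between exit and the end of CRRT fall outside collection. If closing is at the end of CRRT, they fall inside.

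**3. Do the lists match?** The Closing column marks filter life span, mortality, blood loss and packed red cells. The six items of 8.3.3 include none of the four.

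**4. What does the analysis do with a gap?** Under section 11.3.1 a dropped patient of unknown vital status is left out of the ITT set. If the last known status is accepted, the patient may instead be carried forward as alive. Either route lets the loss affect the comparison.

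**5. The protocol's own sample size (section 6.3.2).** Inputs: two-sided α = 0.10, p = 0.50, δ = 0.15, drop-out 5%.

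- n = 1.6449² × 0.5 × 0.5 / 0.15² = 30.06, rounded up to 31.
- 31 / 0.95 = 32.6, rounded up to 33.

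Both stated figures reproduce. In this formula 0.15 is a half-width, so the planned interval spans 30 points.

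**6. Size of the effect on one arm's mortality.** Let d of 33 have unknown vital status, with 50% mortality among the other 33 − d. The lower bound counts all d as alive, (0.5 × (33 − d)) / 33. The upper bound counts all d as dead, (0.5 × (33 − d) + d) / 33. The range is d / 33.

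| d | Observed | Bounds | Range | Half-range |
|---|---|---|---|---|
| 2 | 31 | 47.0% to 53.0% | 6.1 points | ±3.0 |
| 5 | 28 | 42.4% to 57.6% | 15.2 points | ±7.6 |

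Two is about the planned 5% (0.05 × 33 = 1.65). Five is an assumption. Set against the ±15-point tolerance, 7.6 / 15 = 0.51, about half. Any loss beyond two per arm takes the observed number below the planned 31.

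**The case against.** The strongest defence is that the protocol collects more than section 8.3.3 suggests, and much of this stands.

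- The six-item list serves completers as well as discontinued patients. A reader might infer that the four outcomes are not collected for discontinued patients, but that inference would apply to every patient. Sections 8.2.8, 8.2.16 and 8.3.2 collect filter, blood-loss and transfusion data in relation to CRRT, not to nafamostat. The mismatch with the schedule is an inconsistency, not proof of loss.
- A reader might infer that the primary outcome is lost after drop-out. The documents do not support that: note 7 and sections 8.2.15 and 8.3.4 provide for mortality and do not limit it to completers.
- A reader might infer that every stop of the drug is a study exit. Section 9 provides for tapering or stopping it, including for bleeding, without mentioning exit, and section 10.1 itself names stopping medication and stopping observation as two things.
- Renal follow-up is not confined to improved patients. Note 8 and section 8.2.14 set it after CRRT without that condition, and renal recovery is not among the listed efficacy variables.

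These points do not close the gap. General provisions do not say whether they survive an exclusion that takes effect at once. Section 9's silence about exit leaves open which events end participation. That the data may sit in the hospital record makes the remedy easy, but nobody is told to retrieve them.

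**Conclusion.** The point holds in a limited form. Sections 10.1 and 7.4.2 make treatment-related events grounds for leaving the study, and no section states that outcome recording then continues. Closing is undefined for a patient dropped while CRRT continues, so later filter life, blood loss and transfusion may be lost. For mortality the fault is the absence of an explicit statement after drop-out, not a demonstrated loss.

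If vital status were unknown for two of 33, an arm's mortality could move by ±3.0 points, and for five of 33 by ±7.6. These are worst-case bounds at 50% observed mortality. The protocol does not say how many would be lost. It would be wrong to say that five losses use up the whole tolerance: 15.2 points is a full range and the protocol's 15 points is a half-width. Nor does this point alone show that an as-randomised analysis is impossible. The limits on the ITT set in section 11.3.1 are a separate matter.

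**What to change.** Leave unchanged when treatment is stopped, and amend the following:

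1. In section 10.1, separate stopping the assigned treatment from leaving the study. Confine the latter to withdrawal of consent to data collection or true loss to follow-up.
2. State that patients who stop treatment, including those under section 7.4.2, continue to have filter life, blood loss, transfusion, ICU and hospital outcome and 28-day vital status recorded from the hospital record.
3. Reconcile the list in section 8.3.3 with the Closing column in section 8.1.
4. Define one closing time for a patient who stops treatment while CRRT continues.

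The cost is amendment wording and slightly more data abstraction. The patients are inpatients at a single centre, so no visit or procedure is added.
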